## 2. Protocol Description

### 2.1. Study Design

A Randomized Clinical Trial (RCT) will be performed, in which the intervention group will use an application for mobile devices, and the control group will have access to a printed booklet, both with content related to the care of older adults with DM 2. The application for mobile devices developed in a previous study will be applied in this RCT and has the following interfaces: user profile (age, weight, height, Blood Pressure, Blood Glucose, waist circumference), food diary, guidelines and physical exercise plan, record of medications in use, leisure and games (crosswords and word searches) to fix content [30,31].

For the appropriate design of the RCT, the Consolidated Standards of Reporting Trials of Electronic and Mobile Health Applications and online TeleHealth (CONSORT-EHEALTH) and the SQUIRE 2.0 guidelines were used as a basis for the development of the study, considering that these instruments have been recommended by the scientific community, to ensure the validity of the study and applicability of the results [32,33].

### 2.2. Sample Calculation

Considering a α ≤ 5% risk for Type I error, β ≤ 20% risk for Type II error and a power of 80%, estimating an expected reduction after the pre- and post-intervention periods, referring to the use of the application, of 1.24 mg/dL of glycated hemoglobin with a standard deviation of 1.48 mg/dL, an effect size of 0.838 is obtained. In this way, the sample the protocol will be applied to consists of at least 17 older adults with pre-diabetes or DM 2 per group, considering subdivision by extracts and segment losses.

### 2.3. Study Location and Participants

The RCT will be conducted in a Basic Health Unit (BHU) in Ceilândia, Federal District/Brazil, for 3 months by the Health, Care and Aging Research Group (GPeSEn) team at the University of Brasília. This study is part of the GENIOS Project, which develops digital technologies for the self-management of older adults’ health.

The older adults who will participate in the study will be invited through an active search in the Hypertension and Diabetes groups and in routine consultations at the BHU. After applying the inclusion and exclusion criteria (Table 1), they will sign the Free and Informed Consent Form.

### 2.4. Blinding

As an RCT that uses two educational technologies as an intervention, participants will be blinded only regarding the research hypotheses and not regarding the two interventions used. Therefore, blinding regarding randomization, the type of educational technology, and data analysis, pre- and post-intervention, will be applied to the leading researcher and the statistician. The entire process will be conducted by a previously trained and qualified participant from the research group. Blinding will prevent the leading researcher’s biases and prevent differentiated attention to the intervention group.

### 2.5. Application of the Pre-Test

Before distributing the printed booklet to the control group and installing the application on the smartphones of members of the intervention group, the older people who meet the research criteria and sign the informed consent form will respond to a socio-demographic questionnaire, the Diabetes Knowledge Scale (DKN-A), the Diabetes Self-Care Activities Questionnaire (QAD), the Diabetes Self-Efficacy Scale—Short Version (EAD-VC), the Eating Competence Questionnaire, the Determine your Nutrition Questionnaire (DNH) and VIGITEL.

In addition to the instruments that will allow verifying the baseline state of knowledge, self-care, self-efficacy regarding DM and nutritional behaviors of the participants, biochemical blood and urine tests will also be collected, such as: Glycated hemoglobin, fasting blood glucose, lipid profile, serum creatinine and type 1 urine test, according to the IV Brazilian Guideline on Dyslipidemias and Prevention of Atherosclerosis and the Brazilian Diabetes Society.

### 2.6. Randomization and Allocation

As the expected primary outcome will be the reduction in glycated hemoglobin after 3 months of intervention, after obtaining the results of this biochemical parameter in the pre-test period, participants will be randomized and allocated into the intervention and control groups in a stratified manner using the Microsoft Excel program, considering the glycated hemoglobin baseline, so that the values of this parameter are similar in both groups and the sample is homogeneous.

### 2.7. Application of the Intervention

According to the American Association of Diabetes Educators [31], it is necessary to establish a basic education program on diabetes that covers several topics, encouraging self-care and improving quality of life. The main topics of this program include a healthy eating plan, controlling glucose levels, practicing regular physical activity, adhering to medication treatment, and encouraging behaviors that aim to reduce the risk of complications. In this context, the application was created with the aforementioned topics, including weekly notifications of educational and motivational messages validated in a previous study [31] about healthy eating as well as foot care, audios for guided imagery and meditation, healthy recipes aimed at people with diabetes, and games such as “Crosswords” and “Word Search” to reinforce the main topics for diabetes control. The educational booklet was created with the same content as the app, including games such as “Crosswords”, “Word Search”, and “What is the Intruder Food?” [30].

To prepare the content of the topics covered in these educational tools, a bibliographic review was conducted, covering the main Brazilian and global references on the primary care measures aimed at elderly people with diabetes [36,37,38,39,40,41,42,43].

A team of scholarship holders specializing in programming and digital game design was selected to develop the app and the booklet, as well as the images inserted in them, through the University of Brasília’s Notice 01/2022: “Selection of Scholarship Holder for the Research Project Technologies for Health Management and Self-Care for the Elderly—GENIIO-S Project”.

The interventions that will be implemented in this study were developed according to the Contextualized Instructional Design (CID) method. CID refers to a method that aims to describe the planning, development and application of contextualized educational content, and is also used for developing software in the health area CID follows five stages for the systematic construction of educational technologies, namely: analysis, design, development, implementation and evaluation [44]. The CID method was chosen because it meets the work style of the interdisciplinary team that was part of the development of the educational tools developed.

In the Design and Development phases, the following interfaces and sections of the application and booklet were developed, as shown in Table 2.

It is worth noting that both the mobile app and the educational booklet were previously validated by researchers using experts and DM 2 older adults groups [30,31].

During the execution of the clinical trial, older adults in the intervention group (IG) will receive 30–60 min of training on how to use the application, as well as having it installed on their mobile devices by the project team. They will be informed about the continuity of the application surveyed by telephone/messaging application, every fortnight, for three months (intervention time), so that possible doubts about the use of the application can be clarified.

The participants in the control group (CG) will receive an educational booklet previously developed and validated by experts, and its content will address the same themes as the application. At this meeting, the content of the booklet will be presented, in general, for 30–60 min. After the presentation, the researcher will inform the participants that they will take the booklet with them to read, for three months (intervention time), regarding self-care with DM 2.

Regarding the exercises proposed in the application, the adaptation phase will be carried out, which consists of performing the exercises that comprise the aerobic and resistance exercise protocol proposed in the application. Thus, older adults will attend the UBS for two weeks before the intervention phase, on two non-consecutive days a week.

During the 3-month intervention, the following procedures will be carried out:Month 1—resistance exercise protocol twice a week on non-consecutive days, consisting of two series for each exercise and a 30-min walk twice a week.Month 2—resistance exercise protocol twice a week on non-consecutive days, consisting of three series for each exercise and a 30-min walk three times a week.Month 3—resistance exercise protocol twice a week on non-consecutive days, consisting of five series of each exercise and a 30-min walk five times a week.

Both groups (IG and CG) will perform the exercise intervention. All patients will receive the usual treatment (routine consultations with the Unit’s professionals) provided by the BHU, according to their individual needs, which is why the educational intervention should be considered an additional service.

### 2.8. Post-Intervention Procedures (Post-Test)

After 3 months of using the app or educational booklet and the resistance and aerobic exercise protocol, older adults who are part of the GI will answer a questionnaire based on the System Usability Scale (SUS). The SUS is a questionnaire used to evaluate the usability of systems, products, or services. Comprising 10 items, the SUS includes the following statements: 1. “I think I would like to use this system frequently”; 2. “I found the system unnecessarily complex”; 3. “I thought the system was easy to use”; 4. “I think I would need the support of a technical person to be able to use this system”; 5. “I found the various functions in this system were well integrated”; 6. “I thought there was too much inconsistency in this system”; 7. “I would imagine that most people would learn to use this system very quickly”; 8. “I found the system very cumbersome to use”; 9. “I felt very confident using the system”; and 10. “I needed to learn a lot of things before I could get going with this system”) [45].

When comparing the SUS to other instruments used to assess usability, such as the User Interaction Satisfaction Questionnaire (QUIS) and the Usability Metric for User Experience (UMUX), it is clear that the SUS stands out in terms of versatility, as it can be applied to various systems, such as websites, mobile applications, and medical systems, in addition to being simple and easy to apply. The UMUX, despite being a concise instrument like the SUS, differs in that it focuses on the user experience, while the QUIS is more complex, evaluating user interaction through 50 questions [46,47].

Both groups repeat the assessments and laboratory tests carried out in the pre-test to compare the measurements before and after the intervention between and within groups. In this way, it will be possible to evaluate the effect of using the application on older adults. After protocol implementation, both the GI and the GC will have access to the application and the printed booklet. The stages of the clinical trial protocol are described in Figure 1.

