Usability is even more important when a new digital technological tool is developed for people over 60 years old due to the digital literacy barriers they face, such as cognitive decline, decreased visual acuity and lack of familiarity with digital interfaces. Therefore, application design must incorporate usability principles, such as larger fonts that make text readable, simplified navigation, large icons, color contrast, and audio features to make technology more accessible [29].

Therefore, this study aimed to describe a protocol for evaluating the effect of an app for cell phones and tablets on the blood glucose of older adults with DM 2. The protocol aims to compare the effectiveness of an application for mobile devices concerning the educational booklet in reducing Glycated Hemoglobin in older adults with DM 2 in Primary Health Care (PHC).

The primary hypothesis of the study in which this protocol will be applied is that older adults with DM 2 who use the mobile application will have a greater reduction in glycated hemoglobin, and will have a higher level of knowledge, self-care and self-efficacy compared to older adults who use the educational booklet.

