### 2.9. Data Analysis

For data analysis, the Package for the Social Sciences (SPSS^®^) version 20.0 software will be used, in which a database will be built. An initial analysis will be performed to identify typing and classification errors, making corrections when necessary. Statistical tests will be performed as needed. Values of *p* < 0.05 will be considered statistically significant.

Regarding the evaluated and analyzed variables, the nominal qualitative variables are: sex, marital status, place of residence, use of continuous medications, comorbidities, alcoholism, smoking, physical activity, and the presence of cells such as leukocytes and erythrocytes, bacteria, and color in the type 1 urine test. As for the ordinal qualitative variables, the following are considered: education level, urine appearance (e.g., clear, cloudy), and color intensity (e.g., light, dark) in the type 1 urine test, perception of health status, knowledge about diabetes mellitus (DM), level of self-care in DM, and level of self-efficacy in DM. The continuous quantitative variables include: income level, age, weight, height, glycated hemoglobin, fasting glucose, total cholesterol, triglycerides, HDL, LDL, serum creatinine, and type 1 urine test (pH, density, glucose, proteins).

To apply the SUS, the questionnaire is distributed to users after interacting with the system. Responses are scored from 1 to 5, with 1 subtracted from the scores of odd-numbered questions and the scores of even-numbered questions subtracted from 5. This calculation normalizes the scores to a scale from 0 to 4 points. The normalized scores are then summed and multiplied by 2.5, resulting in a final score ranging from 0 to 100. Scores above 68 are considered above average, while scores below indicate a need for improvement. The SUS is valued for its simplicity, flexibility, and ability to compare different systems or versions) [45].

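### Section 2.8 lets within-group before-after change count as evidence of the app's effect, alongside the between-group contrast and unranked against it, although both arms receive the same exercise, usual care and educational content

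*Protocol article*

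**What the plan says.** Section 2.8 has both groups repeat the baseline assessments and laboratory tests "to compare the measurements before and after the intervention between and within groups. In this way, it will be possible to evaluate the effect" of the app in older adults. It names both kinds of comparison and ranks neither.

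Section 2.7 describes what the arms share. On exercise: "Both groups (IG and CG) will perform the exercise intervention". On care: "All patients will receive the usual treatment (routine consultations with the Unit’s professionals) provided by the BHU". On education: "The educational booklet was created with the same content as the app".

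The hypothesis in section 1 is comparative. App users "will have a greater reduction in glycated hemoglobin, and will have a higher level of knowledge, self-care and self-efficacy compared to older adults" given the booklet. Section 2.6 gives the endpoint without a contrast: "the expected primary outcome will be the reduction in glycated hemoglobin after 3 months of intervention". Section 2.9 does not supply one: "Statistical tests will be performed as needed", with p < 0.05 as the threshold. Section 2.2 sizes the trial on "an expected reduction after the pre- and post-intervention periods" with the app, 1.24 with a standard deviation of 1.48.

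**The concern.** A before-after change in the app arm is the sum of whatever the app does and everything else that happens to that arm over three months: an escalating exercise programme, routine consultations, diabetes education and the passage of time. The booklet arm is exposed to the same background. Only the difference between the randomised arms removes it.

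Section 2.8 nevertheless presents the within-group comparison as part of how the app's effect is evaluated, and gives no rule for the case where the two comparisons disagree. A team following the text could report that HbA1c fell significantly with the app and call this the app's effect, even if the booklet arm fell just as far. A shared improvement is plausible, because both arms are given structured exercise and education. What is at stake is a claim for the app that the randomised comparison does not support.

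**Working it through.** **Inputs from the protocol article.** Change with the app 1.24, standard deviation 1.48, at least 17 per group, α 5% (section 2.2); p < 0.05 (section 2.9).

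**Assumptions, not stated in the article.** The 1.48 is the standard deviation of individual change and holds in both arms; tests are two-sided; all 17 per arm are analysed; both arms have the same true fall c, so the app adds nothing over the booklet. Because c is unknown, it is varied from 0.25 to 1.24, in the units of section 2.2.

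**1. The plan's own figure.** 1.24 / 1.48 = 0.838, which reproduces the stated effect size.

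**2. Within-arm paired t-test when the arms do not differ.** With n = 17 there are 16 degrees of freedom and the critical value is 2.120. The noncentrality is c × √17 / 1.48. The probability p of significance comes from the noncentral t distribution.

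**3. App arm significant with a fall, booklet arm not.** The arms are independent, so the chance is p₁ × (1 − p), where p₁ counts significant falls only. At c = 0.25, p₁ is 0.096 and p is 0.100; from 0.50 upwards the two agree to within 0.001.

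| Shared fall c | Noncentrality | App arm significant | App significant, booklet not |
|---|---|---|---|
| 0.25 | 0.70 | 10% | 9% |
| 0.50 | 1.39 | 26% | 19% |
| 0.74 | 2.06 | 49% | 25% |
| 1.00 | 2.79 | 74% | 19% |
| 1.24 | 3.45 | 90% | 9% |

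For example, at 0.74: 0.491 × 0.509 = 0.250. At 1.24: 0.900 × 0.100 = 0.090. A simulation of 200,000 trials at shared falls of 0.25, 0.50, 0.75, 1.00 and 1.24 agrees with these calculations.

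**4. Between-arm test in the same trials.** It is significant in 5% whatever the shared fall, so it falsely favours the app in 2.5%. The simulation gave 4.9% to 5.1%.

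**5. Sensitivity.** The results depend only on c/SD and n. Another standard deviation therefore just rescales the first column: a shared fall of 0.50 with a standard deviation of 0.74 gives the row for 1.00. The 17 is said to allow for losses. If 14 per arm were analysed, the app arm would be significant in 9%, 22%, 41%, 65% and 83% of trials, and the one-arm pattern would occur in 8%, 17%, 24%, 23% and 14%.

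**6. Power of the contrast that should decide.** At 17 per arm the standard error of the difference is 1.48 × √(2/17) = 0.508. If 1.24 is taken as the between-arm difference, the noncentrality is 1.24 / 0.508 = 2.44 and the critical value on 32 degrees of freedom is 2.037. Two-sided power is about 66% without baseline adjustment.

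**The case against.** The strongest reply is that the trial is comparative throughout. Section 2.8 itself plans a between-group comparison and names it first, the hypothesis in section 1 is app versus booklet, and allocation is stratified on baseline HbA1c. Comparing between and within groups is also a common way to describe a group-by-time analysis, which would be valid. And ranking the contrasts is detail that an article may leave to the analysis plan.

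Much of this stands. A reader might infer that the plan has no between-group comparison, or that it will treat significance in one arm only as proof of an effect. The documents support neither: the comparison is planned, and no such rule is stated. The last column of the table therefore prices a misreading that the text permits, not one that it prescribes. Its 25% is also the largest value that p(1 − p) can take; at the article's own 1.24 the figure is 9%.

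A reader might also add regression to the mean to the shared causes of a fall. Table 1 sets no HbA1c threshold for entry, so the article gives no ground for it and the point does not rely on it.

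What the reply does not remove is the affirmative statement in section 2.8, which ties the within-group comparison to evaluating the app. An analysis plan that ranked the contrasts would still leave that sentence to be corrected.

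**Conclusion.** The point holds in this form: section 2.8 accepts within-group change, unranked beside the between-group contrast, as a route to the app's effect, and in this design within-group change cannot show that effect. With no difference between arms, the app arm's own test would be significant in 26% to 90% of trials for shared falls of 0.50 to 1.24, and in 10% at 0.25. A between-group test would falsely favour the app in 2.5%. These figures rest on 17 analysed per arm, a standard deviation of change of 1.48 in both arms, and assumed shared falls.

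It would be too strong to conclude that a misleading within-arm result is the likeliest positive finding. Setting 90% within-arm power against 66% between-arm power uses 1.24 as a change within one arm in the first case and as a true difference between arms in the second, so it does not establish that. That section 2.2 sizes the trial on a pre-post change is a separate matter and adds no weight here.

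**What to change.** In sections 2.8 and 2.9, state that:

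- the effect of the app is judged only by the between-group difference in 3-month HbA1c, with its 95% CI, preferably adjusted for baseline HbA1c, which is already collected and used for stratification;
- within-group changes are descriptive and are not evidence of an app effect;
- the conclusion will be worded as app versus booklet, each added to the same exercise programme and usual care.

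The text change is a few sentences and needs no new data. Section 3 says that the protocol has not yet been implemented, so it can be made before results exist. There are two costs. A within-arm p-value no longer supports a claim. The deciding test, without baseline adjustment, has about 66% two-sided power at 17 per arm if 1.24 is the between-arm difference, short of the 80% in section 2.2. The sample-size statement needs its own review.

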### 2.9. Data Analysis

For data analysis, the Package for the Social Sciences (SPSS^®^) version 20.0 software will be used, in which a database will be built. An initial analysis will be performed to identify typing and classification errors, making corrections when necessary. Statistical tests will be performed as needed. Values of *p* < 0.05 will be considered statistically significant.

Regarding the evaluated and analyzed variables, the nominal qualitative variables are: sex, marital status, place of residence, use of continuous medications, comorbidities, alcoholism, smoking, physical activity, and the presence of cells such as leukocytes and erythrocytes, bacteria, and color in the type 1 urine test. As for the ordinal qualitative variables, the following are considered: education level, urine appearance (e.g., clear, cloudy), and color intensity (e.g., light, dark) in the type 1 urine test, perception of health status, knowledge about diabetes mellitus (DM), level of self-care in DM, and level of self-efficacy in DM. The continuous quantitative variables include: income level, age, weight, height, glycated hemoglobin, fasting glucose, total cholesterol, triglycerides, HDL, LDL, serum creatinine, and type 1 urine test (pH, density, glucose, proteins).

To apply the SUS, the questionnaire is distributed to users after interacting with the system. Responses are scored from 1 to 5, with 1 subtracted from the scores of odd-numbered questions and the scores of even-numbered questions subtracted from 5. This calculation normalizes the scores to a scale from 0 to 4 points. The normalized scores are then summed and multiplied by 2.5, resulting in a final score ranging from 0 to 100. Scores above 68 are considered above average, while scores below indicate a need for improvement. The SUS is valued for its simplicity, flexibility, and ability to compare different systems or versions) [45].

